## SUMMARY

**Rationale:** Insulin resistant subjects and type 2 diabetic patients are characterized by a decreased metabolic flexibility: a reduced capability to switch from fat oxidation in the basal state to carbohydrate oxidation in the insulin-stimulated state. This metabolic inflexibility is an early hallmark in the development of diabetes. Recent evidence suggests that a low carnitine availability may limit acetylcarnitine formation, thereby reducing metabolic flexibility. Thus, when substrate flux in the muscle is high, acetyl-CoA concentrations increase, leading to inhibition of pyruvate dehydrogenase (PDH) and thereby reducing glucose oxidation. The conversion of acetyl-CoA to acetylcarnitine relieves this acetyl-CoA pressure on PDH. To provide more direct insight into the effect of carnitine in preventing metabolic inflexibility and insulin resistance and to further explore the mechanism of action is the focus of this research. Here, we hypothesize that the capacity to form acetylcarnitine may rescue lipid-induced insulin resistance. To this end, insulin resistance will be induced by lipid infusion in healthy volunteers and it will be tested whether carnitine co-infusion can alleviate insulin resistance.

**Objective:** The primary objectives are to investigate whether L-carnitine infusion may rescue lipid-induced insulin resistance and whether L-carnitine infusion is improving metabolic flexibility in the state of lipid-induced insulin resistance. Furthermore, a secondary objective is to examine the molecular pathways of carnitine and acetylcarnitine, responsible for muscle insulin sensitivity.

**Study design:** The current study is an interventional randomized crossover trial in which each subject serves as its own control. Subjects will be blinded for the intervention.

**Study population:** n=13, healthy young (18-40 years) male subjects will be included.

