**Visit 4/5/6 (hyperinsulinemic euglycemic clamp):** During visit 4,5, and 6 a 6-hour hyperinsulinemic euglycemic clamp measurement will be carried out. During each visit (visit 4,5,6) a different trial arm will be tested (trial arm 1: LIPID + CAR, trial arm 2: LIPID + PLAC, trial arm 3: SALINE + PLAC). Subjects will be randomly allocated to the different trials arms. Subjects report to the university after an overnight fast (8PM) at 7AM. We will place an intravenous cannula into the forearm, take a blood sample and begin infusing the glucose tracer (this is part of the preperaring steps for the clamp). Next, we will take the first muscle biopsy. Hereafter, we will continue with a 30 minute indirect calorimetry measurement and the 6-hour hyperinsulinemic euglycemic clamp as described in chapter 8.3. At the end of the clamp we will take a second muscle biopsy of the m. vastus lateralis. The test ends and the subject will receive lunch. The subject will be discharged at 5PM provided blood glucose levels are stable. Three days prior to visit 4,5 and 6, the subjects will be asked to withstand from alcohol, refrain from strenuous physical activity and adhere to their normal eating pattern. During these three days, subjects fill out a food diary to monitor if food intake is equal before the test periods (Appendix F2). Furthermore, subjects will be asked to consume a standardized meal the evening before the 6-hour hyperinsulinemic euglycemic test days (visit 4,5,6), followed by an overnight fast (from 8PM). The meal will be a ready to eat meal "macaroni bolognaise" bought in the local supermarket. Visit 4,5 and 6 will be separated by at least two weeks.

An overview of the entire study is provided in figure 5:

[figure not shown]

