## 6.7 Preparation and labelling of Investigational Medicinal Product

L-Carnitine will be stored as appropriate in the original packaging of the IMP delivered by the AZM pharmacy. At the moment that there will be a subject, the researcher goes to the AZM pharmacy with a prescription for the L-carnitine. The AZM pharmacy will provide the L-carnitine with an delivery label that meets annex 13. Nothing of the L-carnitine is labelled in stock, so a GMP licence is not required.

Natriumchloride 0.9% (as control condition for Intralipid) will be stored as appropriate in the original packaging of the IMP delivered by the AZM. At the moment that there will be a subject, the researcher goes to the AZM pharmacy with a prescription for the natriumchloride. The AZM pharmacy will provide the natriumchloride with an delivery label

that meets annex 13. Nothing of the natriumchloride is labelled in stock, so a GMP licence is not required.

Intralipid will be stored as appropriate in its original packaging of the IMP delivered by the AZM pharmacy. At the moment that there will be a subject, the researcher goes to the AZM pharmacy with a prescription for the Intralipid. The AZM pharmacy will provide the Intralipid with an delivery label that meets annex 13. Nothing of the Intralipid is labelled in stock, so a GMP licence is not required

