### 8.2 Randomisation, blinding and treatment allocation

After inclusion in the study, subjects will be randomly allocated to one of the three interventions arms (saline, intra-lipid, intra-lipid + carnitine). Randomisation will be carried out using an online randomization tool. The intervention arms are labelled according to the subsequent numbers: 1=saline, 2=intra-lipid, 3=intra-lipid+carnitine. The randomisation list is attached in appendix 1A, showing the generated list in excel format. "Set 1" will correspond to the first subject, "set 2" to the second subject and so on. Upon inclusion of a new subject, the subject code will be inserted in consecutive order of inclusion in the excel sheet in the cells that are named "set 1", "set 2" etc.

The leg of the first muscle biopsy of all muscle biopsies will be randomised (left/right). Hereby, potential influence of difference between leg muscle on the outcome will be attenuated. Randomisation will be carried out using an online randomization tool, comparable to the intervention arm randomisation. The legs are labelled according to the subsequent numbers: 1=left leg, 2=right leg. The randomisation list is attached in appendix 1B.

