## **9.2 AEs, SAEs and SUSARs**

### **9.2.1 Adverse events (AEs)**

Adverse events are defined as any undesirable experience occurring to a subject during the study, whether or not considered related to L-carnitine (Carnitene®). All adverse events reported spontaneously by the subject or observed by the investigator or his staff will be recorded.

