### **9.3 Annual safety report**

In addition to the expedited reporting of SUSARs, the sponsor will submit, once a year throughout the clinical trial, a safety report to the accredited METC, competent authority, and competent authorities of the concerned Member States.

This safety report consists of:

- a list of all suspected (unexpected or expected) serious adverse reactions, along with an aggregated summary table of all reported serious adverse reactions, ordered by organ system, per study;
- a report concerning the safety of the subjects, consisting of a complete safety analysis and an evaluation of the balance between the efficacy and the harmfulness of the medicine under investigation.

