blood taken in the entire study will maximally be 538 mL divided over minimal one month. Blood samples are taken via vena puncture or an intravenous cannula. There is a risk of pain, minor bleeding, bruising or inflammation of the sites of the cannulas on the arm. State of the art techniques, measures of sterility and trained personnel minimize these risks. During the anesthesia and muscle biopsies of the upper leg, subjects will experience some pressure and sometimes pain of a short duration. Due to the anesthesia, the procedure will be almost always painless. There is a small risk of infection or prolonged bleeding of the muscle biopsy site. Infections or continued bleeding on the other hand are very rare. To minimize these risk, subjects using anti-coagulants are excluded from the study. A hematoma can develop after taking the biopsy. Sometimes, numbness of small skin-area may persist for some time after the biopsy, due to damaging small cutaneous nerves. The skin incision will result in a small scar (~ 5 mm). To promote good wound healing, the incision will be sealed with sterile steri-strips and a waterproof band-aid. After taking the biopsy compression to the biopsy site will be applied manually and with a compression bandage to minimize bleeding. State of the art technique, measures of sterility and trained personnel will minimize the before mentioned burdens and risks. Furthermore, the risks will be lower in healthy young subjects. After the biopsies, subjects will experience some muscle pain for 2-3 days. Hyperinsulinemic euglycemic clamping is a procedure we perform routinely in our laboratory without notable complications. In rare occasions subjects exhibit symptoms of hypoglycemia (even if their blood glucose levels are still above 3 mmol/l). After successfully performing the clamp procedure, blood glucose values will be monitored for an additional 60 minutes with glucose infusion stand-by, in case glucose levels happen to drop. Solid food and sugar-containing drinks will be provided directly after finalizing the clamp to avoid the experience of hypoglycemia.

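### Passive adverse-event recording in section 9.2.1 may under-report minor subjective and home-onset effects; one scripted question in all three conditions would reduce this

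*Protocol*

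**What the plan says.** - **Recording rule (9.2.1).** "All adverse events reported spontaneously by the subject or observed by the investigator or his staff will be recorded". The definition just before it is wide: "Adverse events are defined as any undesirable experience occurring to a subject during the study, whether or not considered related to L-carnitine". Time at home between visits is therefore in scope.
- **Blinding (Summary).** "Subjects will be blinded for the intervention". No blinding of staff is described. Section 8.2 prints the arm codes ("1=saline, 2=intra-lipid, 3=intra-lipid+carnitine"), Appendix 1A prints the allocation list, and in 6.7 "the researcher goes to the AZM pharmacy with a prescription for the L-carnitine".
- **End of a clamp day (section 3).** "The subject will be discharged at 5PM provided blood glucose levels are stable". Clamp visits are at least two weeks apart, and visit 6 is the last visit in Table 1.
- **Expected effects (10.8 and 12.1 i).** For the infusions: nausea, vomiting, diarrhoea, fishy odour, headache, tiredness and changes in body temperature. For the biopsies: haematoma, numbness and soreness ("After the biopsies, subjects will experience some muscle pain for 2-3 days").
- **Use of the data (9.3).** The annual report includes a report on subject safety, "consisting of a complete safety analysis and an evaluation of the balance between the efficacy and the harmfulness of the medicine" under investigation.
- **Other safeguards.** Section 9.4 follows known events to resolution or stability. There is no safety board (9.5), monitoring is marked as not applicable (11.2), and withdrawn subjects are not followed up (8.6). The only diary in the protocol is for food.

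**The concern.** How adverse events are elicited is normally settled in a protocol's safety section. This protocol does settle it, by a rule that depends on the subject choosing to speak or on staff noticing something. Several of the effects it expects are sensations that staff cannot see, and some may begin or persist after the subject has gone home. The observers can know the condition, whereas the blinded subject, the less biased source, is not put a standard question anywhere in the protocol.

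What is at stake is the quality of the safety description. Section 10.8 cites one earlier study of carnitine given with Intralipid. For the two together during a clamp, it reasons from studies of each infusion given separately. If few events are recorded, the evaluation in 9.3 could take a lack of reports as evidence of good tolerability.

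**Working it through.** The plan states no figure here to reproduce. The check compares the sections, counts exposures and adds a labelled illustration.

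**1. Which expected effects can each route capture?**

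| Effect | Visible to staff? | When expected | Specific to a condition? |
|---|---|---|---|
| Nausea, headache, tiredness | Largely not | During infusion, possibly later | Possibly |
| Vomiting, fishy odour, temperature change | Yes, while on site | During infusion | Possibly |
| Diarrhoea | Only if on site and mentioned | During infusion or later | Possibly |
| Biopsy pain, haematoma, numbness | Partly | Days afterwards | No: two biopsies at every clamp |

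The weak spots are the first and third rows, and anything that starts after discharge. The timing and visibility entries are my reading of 10.8 and 12.1, not statements in the protocol.

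**2. Can observers know the condition?** The protocol does not say so outright. It follows from the named prescription in 6.7, the printed codes in 8.2 and the list in Appendix 1A, together with blinding stated for subjects only.

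**3. How much would a question at each visit cover?**
- Clamp exposures: 13 subjects x 3 = 39.
- Question before discharge: reaches all 39, for effects up to that moment.
- Question on arrival at the next visit: reaches 13 x 2 = 26, each at least 14 days after the clamp.
- No later visit: 39 - 26 = 13 exposures, one third of the total.
- Visit 6 column of Appendix 1A, read with the codes in 8.2:
  - lipid + carnitine: sets 4, 5, 7, 8, 13 = 5 of 13
  - lipid: sets 3, 6, 11, 12 = 4 of 13
  - saline: sets 1, 2, 9, 10 = 4 of 13

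Section 3 numbers the arms in the reverse order. I use the codes in 8.2 because that section introduces the list.

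**4. Illustration of incomplete capture.** Let p be the true risk per carnitine exposure and c the share of cases recorded by any route. Both are assumptions.

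P(none recorded in 13 exposures) = (1 - p x c)^13

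| p | c = 1 | c = 0.6 | c = 0.3 |
|---|---|---|---|
| 0.15 | 0.85^13 = 0.121 | 0.91^13 = 0.293 | 0.955^13 = 0.550 |
| 0.30 | 0.70^13 = 0.010 | 0.82^13 = 0.076 | 0.91^13 = 0.293 |

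A milder case is p = 0.10. The chance of at least one record is 1 - 0.90^13 = 0.746 at full capture and 1 - 0.95^13 = 0.487 at half capture.

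The column c = 1 is an ideal. No questioning scheme reaches it, so the gap to that column overstates what the fix would gain.

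**The case against.** The case for leaving 9.2.1 alone is substantial.

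- **Home-onset effects are not excluded.** A reader might infer that they are lost. The documents do not support that: the definition covers the whole study, and a complaint the subject volunteers is recorded. The text supports possible under-reporting and no more.
- **No comparison of arms is planned.** A reader might infer that a planned safety comparison is biased. Sections 8.1 and 10 contain no safety parameter, and 10.3 is marked as not applicable. The list and summary table in 9.3 cover serious adverse reactions, and serious events have their own reporting route in 9.2.2 and 9.2.3. The point reaches only the overall evaluation in 9.3 and any descriptive listing by condition.
- **Infusion effects should occur under observation.** Section 12.1 j expects carnitine effects to disappear once the infusion stops. Blood is sampled every 5 to 10 minutes during the clamp, and glucose is monitored for 60 minutes afterwards. This narrows the gap. It remains an expectation, however, and passive recording is poorly placed to test it. It also does not help with sensations during the infusion that nobody asks about.
- **Biopsy effects are common to all conditions.** They cannot produce a treatment difference. This stands.
- **A question per visit is not a cure.** This also stands. Nothing follows visit 6, recall elsewhere is at least 14 days, and staff who may know the condition would still ask and record.
- **Questioning may be specified elsewhere.** A case report form or local procedure that is not at hand could contain it. Even so, the rule printed in 9.2.1 is passive, and aligning it would cost little.

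**Conclusion.** The point holds as a modest matter of data quality. Section 9.2.1 states a passive rule and no other section supplements it, so minor subjective effects and effects starting after discharge may be under-reported. The evaluation in 9.3 and any tabulation by condition would then rest on incomplete counts. That observers can know the condition is a sound inference from 6.7, 8.2 and Appendix 1A, not a statement in the protocol.

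The size cannot be derived from the documents. The 12% against 29-55% contrast follows from assumed event and capture rates with perfect capture as the comparator, and should not be read as an estimate. The count that does come from the documents is that 13 of 39 exposures, including 5 of 13 with carnitine, have no later visit at which a question could be asked.

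Section 9.2.1 is not contradicted elsewhere, and the clamp endpoint and its analysis are untouched. This is a worthwhile improvement and not a condition for the trial's validity.

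**What to change.** Amend 9.2.1 along these lines:

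1. In all three conditions, every subject is asked the same scripted, open, non-leading question about how he has felt: before discharge from each clamp visit (since the infusions began) and on arrival at the next visit (since the last one).
2. Each event is recorded with its onset time and its source (elicited, volunteered or observed), and events are listed by condition.
3. After visit 6, either add one brief scripted contact, for example by telephone, or state plainly that events after that discharge are captured only if volunteered. If the contact is added, check that the end-of-study definition in 11.5 (last visit of the last subject) still covers it.
4. Where practicable, let someone unaware of the condition ask the question.

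The cost is a few minutes per visit, one short contact per subject and an extra entry on the case report form. With 13 subjects that means 39 questions before discharge, 26 on arrival and 13 contacts. More minor events will be recorded. Recall over two weeks or more, and the possibility that staff know the condition, remain as limitations.

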### **9.2.2 Serious adverse events (SAEs)**

A serious adverse event is any untoward medical occurrence or effect that

- results in death;
- is life threatening (at the time of the event);
- requires hospitalisation or prolongation of existing inpatients' hospitalisation;
- results in persistent or significant disability or incapacity;
- is a congenital anomaly or birth defect; or
- any other important medical event that did not result in any of the outcomes listed above due to medical or surgical intervention but could have been based upon appropriate judgement by the investigator.

An elective hospital admission will not be considered as a serious adverse event.

The investigator will report all SAEs to the sponsor without undue delay after obtaining knowledge of the events.

The sponsor will report the SAEs through the web portal *ToetsingOnline* to the accredited METC that approved the protocol, within 7 days of first knowledge for SAEs that result in death or are life threatening followed by a period of maximum of 8 days to complete the initial preliminary report. All other SAEs will be reported within a period of maximum 15 days after the sponsor has first knowledge of the serious adverse events.

### **9.2.3 Suspected unexpected serious adverse reactions (SUSARs)**

Adverse reactions are all untoward and unintended responses to an investigational product related to any dose administered.

Unexpected adverse reactions are SUSARs if the following three conditions are met:

1. the event must be serious (see chapter 9.2.2);
2. there must be a certain degree of probability that the event is a harmful and an undesirable reaction to the medicinal product under investigation, regardless of the administered dose;
3. the adverse reaction must be unexpected, that is to say, the nature and severity of the adverse reaction are not in agreement with the product information as recorded in:
  - Summary of Product Characteristics (SPC) for an authorised medicinal product;
  - Investigator's Brochure for an unauthorised medicinal product.

The sponsor will report expedited the following SUSARs through the web portal *ToetsingOnline* to the METC:

- SUSARs that have arisen in the clinical trial that was assessed by the METC;
- SUSARs that have arisen in other clinical trials of the same sponsor and with the same medicinal product, and that could have consequences for the safety of the subjects involved in the clinical trial that was assessed by the METC.

The remaining SUSARs are recorded in an overview list (line-listing) that will be submitted once every half year to the METC. This line-listing provides an overview of all SUSARs from the study medicine, accompanied by a brief report highlighting the main points of concern.

The expedited reporting of SUSARs through the web portal Eudravigilance or ToetsingOnline is sufficient as notification to the competent authority.

The sponsor will report expedited all SUSARs to the competent authorities in other Member States, according to the requirements of the Member States.

The expedited reporting will occur not later than 15 days after the sponsor has first knowledge of the adverse reactions. For fatal or life threatening cases the term will be maximal 7 days for a preliminary report with another 8 days for completion of the report.

### **9.3 Annual safety report**

In addition to the expedited reporting of SUSARs, the sponsor will submit, once a year throughout the clinical trial, a safety report to the accredited METC, competent authority, and competent authorities of the concerned Member States.

This safety report consists of:

- a list of all suspected (unexpected or expected) serious adverse reactions, along with an aggregated summary table of all reported serious adverse reactions, ordered by organ system, per study;
- a report concerning the safety of the subjects, consisting of a complete safety analysis and an evaluation of the balance between the efficacy and the harmfulness of the medicine under investigation.

### **9.4 Follow-up of adverse events**

All AEs will be followed until they have abated, or until a stable situation has been reached. Depending on the event, follow up may require additional tests or medical procedures as indicated, and/or referral to the general physician or a medical specialist.

SAEs need to be reported till end of study within the Netherlands, as defined in the protocol

### **9.5 [Data Safety Monitoring Board (DSMB) / Safety Committee]**

Not applicable.

## 10. STATISTICAL ANALYSIS

For all study parameters data will be reported as minimum, maximum, mean  $\pm$  SD and/or  $\pm$  SEM. Statistical analysis will be performed using the statistical computer program SPSS. The Kolmogorov-Smirnov normality test will be performed to evaluate normality distribution. Pearson correlation coefficients will be computed to correlate parameter values. Differences will be considered significant when  $p < 0.05$ .

Missing values will not be replaced. If a missing value occurs for a specific parameter, the subject in question will not contribute to the analysis of that parameter.

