### 4.4 Sample size calculation

The improvement in insulin sensitivity, determined by a clamp (whole body glucose utilization) combined with carnitine infusion is assumed to be around 0.5 mg/kg/min  $\pm$  0.68 mg/kg/min [7, 11-13], therefore  $\mu=0.5$  mg/kg/min. The variation in the individual improvement upon carnitine infusion is estimated to be 0.68 mg/kg/min ( $\sigma=0.68$ ). Using the following online power calculator for cross-over trials

([http://hedwig.mgh.harvard.edu/sample\\_size/js/js\\_crossover\\_quant.html](http://hedwig.mgh.harvard.edu/sample_size/js/js_crossover_quant.html)), sample size was calculated. To reach a power ( $1-\beta$ ) of 80% and a significance level ( $\alpha$ ) of 0.05 (one-sided) a minimal sample size of N=13 was calculated according to the online power calculator. One-sided testing is adequate as the hypothesis will be tested that carnitine *improves* insulin sensitivity.

Considering a drop-out of 20% ( $(13/100)*20 = 3$  subjects) we will need to include 3 extra subjects in the study, so a total inclusion of 16 subjects. Taking into account exclusion after screening in 30% of the cases, we will need to screen 21 subjects.

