#### **8.4.1 Specific criteria for withdrawal (if applicable)**

Subjects will be withdraw from the study if the research team becomes aware of any of the following conditions:

- non medical reasons (subjects' request or non compliance with the treatment regimen)
- medical reasons considered significant by the subject and/or investigator
- protocol violation

In case of illness or use of medication the subject and/or the principal investigator with the physician will decide whether or not the subject may continue the study.

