### **8.5 Replacement of individual subjects after withdrawal**

Subjects will be replaced after withdrawal

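### The missing-data rule in section 10 deletes a subject's whole record for a parameter, discarding usable crossover data and leaving a completers-only set; the power cost is small and conditional

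*Protocol*

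**What the plan says.** Section 10 rules out imputation and adds: "If a missing value occurs for a specific parameter, the subject in question will not contribute to the analysis of that parameter". The unit removed is the subject, not the visit, and removal is parameter by parameter.

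Section 8.4.1 opens with "Subjects will be withdraw from the study if the research team becomes aware of any of the following conditions". Its list includes non-compliance with the regimen and protocol violation, neither qualified by severity. Section 8.5 reads "Subjects will be replaced after withdrawal", and section 8.6 provides no follow-up afterwards.

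Section 4.4 powers the study on the gain in insulin sensitivity with carnitine. It takes 80% power at a one-sided 5% level, and "a minimal sample size of N=13 was calculated". It then adds 3 subjects for 20% drop-out, giving 16 inclusions. Section 10.1 analyses insulin sensitivity by a two-way repeated-measures ANOVA over the three conditions and time, and metabolic flexibility by a one-way ANOVA over the three conditions.

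**The concern.** The carnitine question is answered within subjects by the two lipid visits. SALINE+PLAC shows how much insulin resistance the lipid induces, but it is not part of that difference. Under the rule, a lost saline clamp still removes an intact LIPID+CAR/LIPID+PLAC pair. For metabolic flexibility, the basal and insulin-stimulated hood sessions at all three visits must succeed, six in total, or the subject leaves that analysis.

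The second issue is selection. A subject withdrawn part-way has missing visits, so the rule removes his completed clamps and a new subject takes his place. Only subjects are described as blinded, and the protocol prints the sequence list in Appendix 1A. Who remains in the analysis can therefore depend on decisions taken after randomisation by staff with access to the allocation, and on events that may differ by condition. Replacement restores the count but does not remove that selection.

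**Working it through.** **Inputs (section 4.4).** Mean gain 0.5 mg/kg/min ("combined with carnitine infusion is assumed to be around 0.5 mg/kg/min"); SD of the individual gain 0.68 mg/kg/min ("The variation in the individual improvement upon carnitine infusion is estimated to be 0.68 mg/kg/min"); one-sided alpha 0.05; power 80%; N = 13; 16 inclusions.

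**Step 1: reproduce the plan's figure.** For a one-sided paired t-test on n subjects, power = P(T > t(0.95, n−1)), where T is noncentral t with n−1 degrees of freedom and noncentrality (0.5/0.68)·√n. At n = 13 the noncentrality is 0.7353 × 3.606 = 2.651 and the critical value is 1.782, so power is 80.3%. N = 13 is reproduced. Nearby values are 77.1% at 12, 73.4% at 11, 69.2% at 10 and 87.7% at 16. Each subject lost below 13 costs 3 to 4 points.

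**Step 2: isolate what the rule costs.** Missing visits lose information under any analysis. The rule's own cost is the gap between needing all three clamps and needing only the two lipid clamps. Let each clamp fail independently with probability f. The protocol gives no rate, so f is an assumption.

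- Subjects kept under the rule: N(1−f)³
- Subjects with both lipid visits: N(1−f)²

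With f = 5% and N = 13: 13 × 0.95³ = 11.1 against 13 × 0.95² = 11.7, a difference of about 0.6 of a subject.

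Averaging the Step 1 power over a binomial number of analysable subjects, with success probability (1−f)³ or (1−f)², gives:

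| Subjects available | f (assumed) | Power, all three clamps needed | Power, both lipid clamps needed | Cost of the rule (points) |
|---|---|---|---|---|
| 13 | 1% | 79.0% | 79.5% | 0.4 |
| 13 | 5% | 73.5% | 75.8% | 2.3 |
| 13 | 10% | 66.0% | 70.9% | 4.9 |
| 16 | 5% | 82.0% | 84.0% | 2.0 |
| 16 | 10% | 75.1% | 79.7% | 4.5 |

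Most of the fall from 80.3% in the 13-subject rows comes from the missing clamps themselves. The last column is the part due to the rule. The right-hand power column counts intact lipid pairs only; it is not an exact power for a mixed model.

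**Step 3: the drop-out allowance.** 16 × 0.80 = 12.8, about 13. If drop-out is random at 20% with no replacement, the chance that at least 13 of 16 complete is 0.60 and average power is 79.1%. With replacement, 13 completers are restored.

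**Step 4: metabolic flexibility.** With an assumed 5% failure per hood session, 13 × 0.95⁶ = 9.6 subjects stay under the rule, against 13 × 0.95⁴ = 10.6 with both lipid visits intact. These are counts only. Section 4.4 powers clamp glucose utilisation and makes no power claim for the change in RER.

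**The case against.** The best defence is that the plan already protects its sample size. It includes 16 subjects and replaces those withdrawn, and complete-case repeated-measures ANOVA is a coherent choice when visits are few. Exclusion is also by parameter, so a failed hood session leaves GIR and Rd untouched. All of this stands, and it limits the power argument. It does not answer the loss of intact lipid pairs or the selection of completers. The margin is also not carried through consistently: the Summary and section 4.1 give 13 subjects, and Appendix 1A lists 13 sequences.

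A reader might infer three stronger things:

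- **That the trial must fall below 80% power.** The documents do not show this. Starting from 16 with 5% clamp failure, average power under the rule is 82.0%. A shortfall requires the extra subjects to be used up or never enrolled, or a higher failure rate.
- **That one missing time point within a clamp deletes the subject.** With 12 values per subject and 1% to 5% missing (both assumptions), only 11.5 to 7.0 of 13 would remain. The protocol does not say how many time points enter the ANOVA or whether the rule applies at that level, so this cannot be counted.
- **That carnitine or lipid intolerance will bias the result.** No rate is given, and section 10.8 describes the side-effect risk as small. Selection is made possible, not demonstrated.

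Two links are also inference. The loss of withdrawn subjects' clamps follows from applying the section 10 rule to them; no separate sentence says so. Nor does the protocol say whether a failed clamp in a continuing subject is repeated or leads to replacement.

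**Conclusion.** The point holds as a criticism of a stated rule. The rule discards usable within-subject data from the key comparison and, combined with withdrawal and replacement, leaves a completers-only set shaped by post-randomisation events. The size is modest. With 13 subjects available and an assumed, independent 5% clamp failure, the rule itself costs about 0.6 of a subject and about 2 power points (73.5% against 75.8%). The cost runs from 0.4 points at 1% failure to 4.9 at 10%. With 16 subjects and 5% failure, power stays near 82%. These figures rest on the plan's 0.5 and 0.68 and its one-sided test. The selection issue cannot be quantified from the document. It is worth correcting because the change is cheap, not because the trial is invalid without it.

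**What to change.** Replace the deletion rule in section 10 by a linear mixed model with condition and period as fixed effects, subject as a random effect, and small-sample degrees of freedom (Kenward-Roger or Satterthwaite). The model should use every available visit, including valid completed clamps of subjects who are later withdrawn or replaced. Name LIPID+CAR minus LIPID+PLAC as the planned contrast. State beforehand what makes a completed clamp valid, so that a clamp affected by the violation itself is not kept by default. Report completers-only results as a sensitivity analysis, and list withdrawals by the last condition received. The withdrawal and replacement rules need not change.

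The cost is slightly more analysis work, and a covariance structure and degrees-of-freedom method to fix in advance for a small sample. The model assumes that data are missing at random, which the completers-only sensitivity analysis and the listing of withdrawals would help a reader to judge.
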